## Abstract

**Background::**

Vascular dementia (VaD) is the second most common cause of dementia. The treatment of VaD still remains a challenge so far. Traditional Chinese Herbal medicine is a promising therapy due to their multiple components and targets. Shenmayizhi decoction (SMYZD), a Chinese Herbal prescription, has been reported its effective in alleviating cognitive dysfunction in clinical practice. However, strong clinical research of SMYZD in the treatment of VaD was lack. Therefore, we design this study to evaluate the adjuvant role of SMYZD in the treatment of VaD.

**Methods::**

This is a multicenter, randomized, blind, controlled trial. A total of 196 eligible patients will be assigned to receive Ginkgo biloba extracts (GBEs) plus SMYZD granule or GBEs plus SMYZD mimetic granule in a 1:1 ratio. The duration of the trial will be 12 weeks, and a follow-up will be performed at the 24th week. The primary outcomes are the National Institute of Health stroke scale (NIHSS) and the Alzheimer Disease Assessment Scale-cognitive subscale (ADAS-cog). The secondary outcomes include the Mini-Mental State Examination (MMSE), the traditional Chinese Medicine (TCM) syndrome scale, Activities of Daily Living (ADL), concentrations of hypersensitive C-reactive protein (Hs-CRP), neuron-specific enolase (NSE) and homocysteine (HCY) in serum. Researchers will record any adverse events throughout the trial.

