#### Exclusion criteria

2.3.2

Patients meet the following criteria will be excluded:

(1)Depression (Hamilton Depression Scale 17 score ≥7) or other mental disorders;(2)Dementia caused by other diseases (eg, Alzheimer disease, epilepsy, encephalitis, Parkinson disease, trauma);(3)Severe visual and hearing impairment, severe aphasia or limb dysfunction might affect assessment;(4)Thyroid disease, vitamin deficiency or severe disease (severe heart, liver, renal system disease, cancer);(5)Use of other drugs (including herbal medicine) that exhibit any known actions on the central nervous system within 3 months before baseline;(6)Allergic to herbal medicine or Ginkgo biloba extracts;(7)Currently participating in another clinical trial.

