### Sample size calculation

2.5

The sample size was calculated based on the mean change from baseline in the Alzheimer Disease Assessment Scale-cognitive subscale (ADAS-cog) score. The previous study show that 1.5-point could detect a difference on ADAS-cog,^[33]^ thus we set δ = 1.5. With α at 0.05, β = 0.2 (80% power), s = 3.5, and δ = 1.5. As a result, 85 participants were needed in each group. Considering a discontinuation of 15%, the sample size required for the study was 98 per group.

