#### Primary outcomes

2.10.1

1.The changes in cognitive function will be assessed by Alzheimer Disease Assessment Scale-cognitive subscale (ADAS-cog).^[35]^ The total score of ADAS-cog ranges from 0 to 70, and a higher score indicates more severe dysfunction.2.The neurological status will be evaluated by National Institute of Health stroke scale (NIHSS).^[36]^ The maximum score of NIHSS is 42, and a higher score represents more severe neurological deficit.

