### Statistical analysis

2.13

All the data will be analyzed by a statistician using SPSS 19.0 software (IBM Corp., Armonk, NY) in a blinded manner. Outcomes will be analyzed in accordance with the intention-to-treat (ITT) principle. Missing values will be handled by the multiple imputation method.^[40]^ Homogeneity of Baseline characteristics will be analyzed with *t* test for continuous variables and χ^2^ test for categorical variables, or with Wilcoxon Mann–Whitney test. Primary outcomes, and secondary outcomes will be analyzed by covariance with treatment groups as factors and baseline values as covariates. Mean difference will be used to illustrate the effect size.

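### Two unranked primary outcomes but a sample size for ADAS-cog alone: the planned 5% error and 80% power hold together only if ADAS-cog carries the primary conclusion

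*Protocol article*

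**What the plan says.** Two outcomes have primary status. The Abstract (Methods) says: "The primary outcomes are the National Institute of Health stroke scale (NIHSS) and the Alzheimer Disease Assessment Scale-cognitive subscale (ADAS-cog"). Section 2.10.1 (Primary outcomes) lists ADAS-cog first and then NIHSS: "The neurological status will be evaluated by National Institute of Health stroke scale (NIHSS"). The order differs between the two places, and nothing in either ranks one scale above the other.

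Only one of them is used for sizing. Section 2.5 (Sample size calculation): "The sample size was calculated based on the mean change from baseline in the Alzheimer Disease Assessment Scale-cognitive subscale (ADAS-cog) score". The inputs are "With α at 0.05, β = 0.2 (80% power), s = 3.5, and δ = 1.5", followed by "As a result, 85 participants were needed in each group" and "Considering a discontinuation of 15%, the sample size required for the study was 98 per group". No effect, standard deviation or power is given for NIHSS.

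Section 2.13 (Statistical analysis) treats primary and secondary outcomes alike: they "will be analyzed by covariance with treatment groups as factors and baseline values as covariates". It gives no order of testing, no division of α, and no statement on whether one or both primary outcomes must succeed.

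**The concern.** A sample size calculation promises an error rate and a power for a particular conclusion. Here the calculation is for one outcome, while the trial's primary conclusion is attached to two. With two unranked primary outcomes there are two natural ways to declare success, and the plan's 5% and 80% do not both survive under either of them:

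- If one positive scale is enough, there are two chances of a false positive and the error exceeds 5%.
- If both scales must be positive, the error is controlled, but the power is that of winning twice, which is below the power of winning on ADAS-cog alone.

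What is at stake is the reading of a split result. If ADAS-cog is positive and NIHSS is not, or the reverse, this document does not say whether the trial succeeded.

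**Working it through.** **Inputs.** From section 2.5: δ = 1.5, s = 3.5, α = 0.05, power 80%, 85 evaluable and 98 randomized per group, 15% discontinuation. Allocation is 1:1 (section 2.1). Sidedness of α is not stated. NIHSS power and the correlation r between the two test statistics are not given, so both are assumptions here and shown as ranges.

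**Step 1: reproduce the plan's figure.**
n per group = 2(z₀.₉₇₅ + z₀.₈₀)² s²/δ² = 2 × (1.960 + 0.842)² × 3.5²/1.5² = 85.47.
This agrees with the stated 85. A one-sided 5% test would need 68, so the plan has used two-sided 0.05 on one outcome. For dropout, 85 × 1.15 = 97.75, rounded up to 98. Dividing by 0.85 would give 100, a small difference that does not affect this point.
Power at 85 per group: δ/(s√(2/85)) = 2.794, and Φ(2.794 − 1.960) = 79.8%. The ADAS-cog claim is sound taken alone, and it uses the whole of α.

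**Step 2: success on either outcome.** Each scale is tested at two-sided 0.05 with no true effect on either. The chance of at least one significant result is 1 − P(|Z₁| ≤ 1.96 and |Z₂| ≤ 1.96). At r = 0 this is 1 − 0.95² = 9.75%. Counting only false positives in favor of treatment gives 1 − 0.975² = 4.94% at r = 0, against 2.5% for one test.

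**Step 3: success on both outcomes.** If NIHSS had the same power at 85 per group as ADAS-cog (assumed), joint power at r = 0 is 0.798² = 63.7%. For r > 0 it comes from the bivariate normal distribution.

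| r | Either: false positive, any direction | Either: false positive for benefit | Both: joint power at 85 per group |
|---|---|---|---|
| 0 | 9.75% | 4.94% | 63.7% |
| 0.3 | 9.51% | 4.76% | 66.3% |
| 0.5 | 9.07% | 4.54% | 68.4% |
| 0.8 | 7.81% | 3.90% | 72.6% |
| 0.9 | 7.04% | 3.52% | about 75% |

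The joint power depends on the assumed NIHSS power. With ADAS-cog at 80% and r from 0 to 0.8, it is 40% to 49% if NIHSS power is 50%, and 72% to 78% if NIHSS power is 90%. It can never exceed the ADAS-cog power.

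**Step 4: α split to protect an either-outcome claim.** At two-sided 0.025 for ADAS-cog, power at 85 per group is Φ(2.794 − 2.241) = 71.0%, or 70.3% with the t distribution. Restoring 80% needs 2 × (2.241 + 0.842)² × 3.5²/1.5² = 103.5, so 104 evaluable per group, or 104/0.85 = 123 randomized against the planned 98.

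**Step 5: ADAS-cog first.** If ADAS-cog is tested at 0.05 and NIHSS only after ADAS-cog succeeds, the family-wise error stays at or below 5% and ADAS-cog keeps the power of Step 1. This, or ADAS-cog as the sole primary outcome, is where the plan's two figures hold together.

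**The case against.** The strongest reply is that a multiplicity rule is ordinary content for a statistical analysis plan, that this is a condensed article, and that its silence therefore proves nothing. Part of this stands. An unseen plan could add a fixed sequence starting with ADAS-cog, which would preserve both figures, so the absence of a rule is not by itself the finding. What remains is stated in this document: two primary outcomes without rank, and a sample size that gives all of α to one of them and no power to the other. An analysis plan that split α or required both outcomes would undercut section 2.5. One that put ADAS-cog first would add a ranking that the Abstract and section 2.10.1 do not give. In each case this text needs a line of correction.

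It is also fair to say that section 2.5 claims its 5% and 80% for ADAS-cog only, and that this claim reproduces.

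A reader might infer more than the document supports:

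- **That error and power both fail at once.** They do not. Under an either-outcome rule the chance of at least one success is not below the ADAS-cog power. Under a both-outcomes rule the error is at or below 5%.
- **That NIHSS has a floor and cannot improve here.** Section 2.3.2 excludes patients whose "severe aphasia or limb dysfunction might affect assessment", but milder deficits remain eligible and no baseline NIHSS distribution is given.
- **That week 24 adds two more chances to win.** The article calls week 24 a follow-up and nowhere makes it a basis for the primary claim. The visit schedule table is not shown.
- **That the success rule will be picked after seeing the data.** Nothing says so. Section 2.12 describes locking the database after a blinding check, and section 2.13 describes a blinded analysis.

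**Conclusion.** The point holds in a limited form. The ADAS-cog calculation is correct for ADAS-cog, but it does not describe a primary conclusion that rests on two unranked outcomes. Under an either-outcome rule the error is about 7.0% to 9.75% instead of 5%. Under a both-outcomes rule the power is below the ADAS-cog power of about 80%: roughly 64% to 75% if NIHSS has similar power, and lower if NIHSS power is lower.

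The error range rests only on normal theory and a correlation between 0 and 0.9. The joint-power range also rests on an assumed NIHSS power, because the document gives no NIHSS effect or standard deviation. A joint-power figure for this trial therefore cannot be computed from the document. The qualitative conclusion needs neither assumption: the planned pair of 5% and 80% is kept only if ADAS-cog alone, or ADAS-cog first in a fixed sequence, carries the primary conclusion.

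**What to change.** By amendment while the trial is still blinded:

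1. State that the primary conclusion rests on the change in ADAS-cog from baseline to week 12, the end of treatment, tested at two-sided 0.05.
2. State that NIHSS is tested at two-sided 0.05 only if ADAS-cog is significant. NIHSS may stay listed as a primary outcome in second place in the sequence, or become the first secondary outcome.
3. State in section 2.5 that α is two-sided and that the 80% power refers to ADAS-cog only.
4. Carry the same order through the Abstract, section 2.10.1, section 2.13, the registry entry and any analysis plan.

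This needs no further patients or data and matches the existing sample size. It is a change to the status of a published primary outcome during recruitment (section 2.4 says recruitment is under way), so it should be dated and recorded as made blind. The real loss is that NIHSS alone can no longer support a positive claim.

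If the sponsor prefers another rule, the trial must be re-sized to match. An even α split needs 104 evaluable per group for ADAS-cog. Requiring both needs a justified NIHSS effect and standard deviation first. As an illustration only, if NIHSS had the same standardized effect as ADAS-cog and the tests were independent, 80% joint power needs √0.80 = 89.4% power on each, or 113 evaluable per group (113/0.85 = 133 randomized).

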**Discussion::**

This study will provide evidences to evaluate the efficacy and safety of SMYZD in combination with GBEs in treatment of VaD, as well as the adjuvant role of SMYZD in combination.

**Trial is registered at Chinese Clinical Trial Registry::**

ChiCTR1800017359.

## Introduction

1

Vascular dementia (VaD) is the secondary cause of dementia after Alzheimer disease and accounts for 15% of all cases of dementia worldwide.^[1]^ In China, the prevalence of VaD is 1.50% for those aged over 65 years.^[2]^ Effective interventions or treatments to reduce the burden of VaD are urgently needed. However, no definitive medications or satisfactory pharmacological therapies have been introduced for the treatment of VaD. Currently, treatments are mainly focused on easing psychiatric symptoms or preventing cerebrovascular risk factors. Cholinesterase inhibitors and glutamate receptor antagonists have shown modest cognitive benefits in patients with VaD, yet they have not reached the expected therapeutic effects. In addition, their side effects are significant. Therefore, it is essential to develop and evaluate new promising treatments for VaD.

Traditional Chinese medicine (TCM) is drawing the researchers’ attention for its abundant experiences in the treatment of dementia. According to the theory of TCM, qi deficiency, blood stasis and hyperactivity of the liver yang are significant pathological factors of VaD. SMYZD is a compound formula with functions of supplementing qi, activating blood circulation, calming the liver and suppressing liver yang. Our preclinical pharmacological experiments have shown that SMYZD granule promoted neurovascular unit angiogenesis by enhancing hypoxia inducible factor 1 α, vascular endothelial growth factor and notch protein expression, and exerted anti-oxidative stress effects by regulating the Nrf2/HO-1 signaling pathway and anti-apoptotic effects though reducing the expression of caspase 3.^[3]^ SMYZD consists of four herbal drugs, including *Radix et rhizome Ginseng* (Ren Shen), *Rhizoma Gastrodiae* (Tian Ma), *Rhizoma Chuanxiong* (Chuan Xiong) and *Ramulus Euonymi* (Gui Jian Yu), the corresponding pharmacological targets of these herbs are listed in Table 1, which could be involved in the management of VaD.

**Table 1 T1:**
[figure not shown]
Multitarget mechanisms of SMYZD.

A pilot trial had been conducted to explore the efficacy of SMYZD, however, the pilot study was limited by the small sample size and absence of follow-up. The GBEs is believed to be effective and safe in the treatment Alzheimer disease and VaD.^[28,29]^ Therefore, the present study aims to evaluate the efficacy and safety of SMYZD as an adjuvant treatment for VaD using a randomized, controlled, blind and multicenter trial.

## Methods

2

### Study design

2.1

This study is a multicenter, randomized, blind, controlled trial with a 1:1 allocation. The present protocol was registered at Chinese Clinical Trial registry (Number: ChiCTR1800017359) on July 25, 2018, and we design this protocol in accordance with the Standard Protocol Items: Recommendation for Interventional Trials 2013.

After a recruitment period and obtaining the signed informed consent from all the participants, eligible participants will be randomized to SMYZD group or control group, and receive treatment for 12 weeks, with a follow-up assessment at 24th week. A flowchart of the study is shown in Fig. 1. The evaluations and visits will be conducted according to the testing schedule as shown in Table 2.

**Figure 1 F1:**
[figure not shown]
Flowchart of the study.

**Table 2 T2:**
[figure not shown]
Schedule of the study process.

### Ethics approval and consent to participates

2.2

The study protocol (version 1.1, date November 6, 2017) was approved by the ethics committees of the Xiyuan Hospital, China Academy of Chinese Medical Science (the sponsor of this study, approval number: 2017XLA033–4). The trial was registered at Chinese Clinical Trial Registry (Number: ChiCTR1800017359). The study's aims, procedures and possible side effects will be explained to the participants. Singed informed consent will be obtained from all the participants. No participants’ names or identifying information will be released.

### Participants

2.3

#### Inclusion criteria

2.3.1

Patients will be enrolled in this trial if they meet the following criteria:

(1)Patients 45≤ aged ≤ 75, male or female, and females should be post menopause;(2)Clinical diagnosis of VaD according to the Diagnostic and Statistical Manual of Mental Disorders IV (DSM-IV)^[30]^ and NINDS-AIREN^[31]^;(3)Clinical Dementia Rating (CDR) score of 1 to 2;(4)MMSE score of 10 to 26;(5)Hachinski Ischemic scale (HIS) score ≥7;(6)Diagnosis of qi deficiency, blood stasis and hyperactivity of the liver yang syndrome according to Guiding Principle of Clinical Research on New Drugs of Traditional Chinese medicine (Trial).^[32]^(7)Adequate intellectual function to provide voluntary signed informed consent.

#### Exclusion criteria

2.3.2

Patients meet the following criteria will be excluded:

(1)Depression (Hamilton Depression Scale 17 score ≥7) or other mental disorders;(2)Dementia caused by other diseases (eg, Alzheimer disease, epilepsy, encephalitis, Parkinson disease, trauma);(3)Severe visual and hearing impairment, severe aphasia or limb dysfunction might affect assessment;(4)Thyroid disease, vitamin deficiency or severe disease (severe heart, liver, renal system disease, cancer);(5)Use of other drugs (including herbal medicine) that exhibit any known actions on the central nervous system within 3 months before baseline;(6)Allergic to herbal medicine or Ginkgo biloba extracts;(7)Currently participating in another clinical trial.

### Recruitment

2.4

Participants will be recruited from Xiyuan hospital and community healthcare centers of Jingzhuang Town and Shen Jiaying Town, Yanqing District, Beijing. The enrollment will be advertised through hospital posters and oral promoting by researchers. The recruitment is now on-going. Eligible participants will sign the informed consent form and receive a copy one which contains the contact telephone of the investigator. A dedicated phone line will response inquiries about joining in the project (8 am to 6 pm, from Monday to Friday).

### Sample size calculation

2.5

The sample size was calculated based on the mean change from baseline in the Alzheimer Disease Assessment Scale-cognitive subscale (ADAS-cog) score. The previous study show that 1.5-point could detect a difference on ADAS-cog,^[33]^ thus we set δ = 1.5. With α at 0.05, β = 0.2 (80% power), s = 3.5, and δ = 1.5. As a result, 85 participants were needed in each group. Considering a discontinuation of 15%, the sample size required for the study was 98 per group.

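### The sample-size figures in section 2.5 do not agree: 98 per group less 15% leaves about 83, not the 85 stated as needed, a minor shortfall of 1 to 1.6 points of power

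*Protocol article*

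**What the plan says.** Section 2.5 sizes the trial on one of the two primary outcomes: "The sample size was calculated based on the mean change from baseline in the Alzheimer Disease Assessment Scale-cognitive subscale (ADAS-cog) score". The inputs are printed in one line: "With α at 0.05, β = 0.2 (80% power), s = 3.5, and δ = 1.5". The result before any allowance for loss is "As a result, 85 participants were needed in each group". The allowance follows: "Considering a discontinuation of 15%, the sample size required for the study was 98 per group". The Abstract carries the doubled figure: "A total of 196 eligible patients will be assigned", in a 1:1 ratio.

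The article does not say whether α is one- or two-sided, which formula was used, how the result was rounded, or how the 15% was applied. Section 2.13 plans an intention-to-treat analysis with multiple imputation of missing values, and an analysis of covariance with the baseline value as covariate.

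**The concern.** A sample-size formula returns a minimum, so a fractional result is rounded up. An allowance for loss is meant to leave that minimum after the loss has occurred, so the minimum is divided by the proportion retained. Multiplying by one plus the loss proportion always gives too few, because the loss is then taken from a larger number than the one it was calculated on.

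Section 2.5 appears to do the opposite at both steps, and the two slips run in the same direction. At stake is whether the stated 80% power follows from the stated inputs and the stated discontinuation rate. All the figures needed to check this are printed, so the point does not depend on detail that a journal article leaves to the full protocol.

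**Working it through.** **Inputs, all from section 2.5:** δ = 1.5, s = 3.5, α = 0.05, power 80%, discontinuation 15%. Allocation is 1:1 (section 2.6).

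**Step 1. Reproduce the 85.**
n per group = 2 × (z for α + z for power)² × s² / δ²
- Two-sided: 2 × (1.960 + 0.842)² × 3.5² / 1.5² = 85.47.
- One-sided: the same formula gives 67.3.

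Only the two-sided reading comes near 85, so two-sided α is inferred. The stated 85 is 85.47 rounded down. Rounded up it is 86; the noncentral t calculation needs 87.

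**Step 2. Reproduce the 98.**
- Multiplying: 85 × 1.15 = 97.75, which rounds to 98. This matches the article.
- Dividing: 85 / 0.85 = 100. This does not match.

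**Step 3. Check the printed figures against each other.** This step needs no assumption about how the 98 was obtained.
- 98 × (1 − 0.15) = 83.3 per group, below the stated need of 85.
- Largest loss that still leaves 85: (98 − 85) / 98 = 13.3%.
- Largest loss that still leaves 86: (98 − 86) / 98 = 12.2%.

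**Step 4. Requirement with the slips corrected.**

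| Evaluable per group | Divided by 0.85 | Randomised per group | Total |
|---|---|---|---|
| 85 (dropout step only) | 100 | 100 | 200 |
| 86 (rounding also corrected) | 101.2 | 102 | 204 |
| 87 (t test) | 102.4 | 103 | 206 |

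Against 98 per group, the gap is 2 to 5 per group.

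**Step 5. Power for an unadjusted comparison of two means.**
Normal approximation: power = Φ( δ / (s × √(2/n)) − 1.960 ). For n = 83.3 this is Φ(2.766 − 1.960) = Φ(0.806) = 79.0%.

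| Evaluable per group | Normal approximation | t test |
|---|---|---|
| 83 | 78.8% | 78.4% |
| 83.3 | 79.0% | 78.5% |
| 85 | 79.8% | 79.3% |
| 86 | 80.2% | 79.8% |
| 87 | 80.7% | 80.3% |
| 98 (no loss) | 85.1% | 84.7% |

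After the stated 15% loss, power is therefore 78.4% to 79.0%, which is 1.0 to 1.6 points below 80%.

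**Step 6. What baseline adjustment would have to recover.** Adjustment multiplies the residual variance by 1 − r², where r is the correlation between the change score and baseline. The r that restores 80% is:
- normal approximation: r² = 1 − 83.3/85.47 = 0.025, so r is about 0.16;
- t test: r² = 1 − 83/86.44 = 0.040, so r is about 0.20.

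The article gives no value of r. These are the values that would be needed, not estimates.

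**The case against.** The strongest reply is that the effect is immaterial. Each slip alone is tiny: 85 instead of 86 gives 79.8% power by the normal approximation, which rounds to the stated 80%, and 98 instead of 100 is two participants per group. Even together they cost less than 2 points. This stands, and it is why the point is minor.

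A second reply is that the power above belongs to an unadjusted comparison of participants with data, whereas section 2.13 plans a baseline-adjusted analysis. This also stands in part: a correlation of 0.16 to 0.20 would close the gap. However, section 2.5 claims no such gain and gives no correlation, so the printed calculation cannot rely on it.

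A third reply is that discontinuation need not mean missing outcomes. The dropout list in section 2.8 includes poor compliance and prohibited medication, and under intention to treat such participants may still be assessed. The article leaves this open, so 83 is the figure if all 15% lack outcome data. Multiple imputation does not in general replace the information lost with a missing outcome, and section 2.5 itself treats discontinuation as something to enlarge the sample for.

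Finally, the multiplication by 1.15 is an inference, because no formula is printed. That is correct, but the conflict in step 3 does not depend on it.

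A reader might go further and infer that the trial is materially underpowered, that it has no reserve, or that 102 per group is the one correct target. The documents support none of these. The shortfall is at most 1.6 points, baseline adjustment is a possible reserve, and the requirement is 100, 102 or 103 depending on rounding and formula.

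**Conclusion.** The point holds as a minor arithmetic error. A need of 85, a 15% discontinuation and a requirement of 98 cannot all be right, and the 85 is itself rounded down from 85.47. If 15% of participants have no outcome data, about 83 per group remain, with about 78% to 79% power for an unadjusted comparison.

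This rests on two-sided α (inferred from the 85), on the article's δ and s taken as given, and on all discontinued participants lacking outcome data. It says nothing against the planned analysis or the validity of the trial. The error lies in the stated figures.

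**What to change.** Correct section 2.5 and keep the total of 196. Either of two statements would be accurate:

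- 98 per group leaves about 83 evaluable after 15% discontinuation, with about 78% to 79% power (two-sided α = 0.05) before baseline adjustment; or
- 98 per group allows for about 13% discontinuation if 85 evaluable participants are needed, or about 12% if 86 are needed.

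The sentence should also name the sidedness and the method used for the dropout allowance, so that a reader can reproduce the figure. If the sponsor wishes to rely on baseline adjustment to reach 80%, the assumed correlation should be stated.

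The cost is one edited sentence and a slightly less favourable stated figure. Section 2.4 says recruitment is under way; neither statement needs extra enrolment.
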